### Training of HEMS personnel

Training is key for all high-stakes procedures, especially under time constraints. Given that the capacity to train all HEMS teams at the same time is limited, a stepped-wedge design was chosen (Fig. 3) [11, 12].

**Fig. 3 Fig3:**
[figure not shown]
Schematic timetable of the stepped-wedge study design. ECPR experienced personnel and non-ECPR experienced personnel). HEMS: Helicopter Emergency Medical Service. CCPR: HEMS operating without ECMO: Conventional CardioPuImonary Resuscitation. ECPR: HEMS operating with ECMO: Extra-Corporeal CardioPulmonary Resuscitation Training: Timing training of HEMS personnel

This design also prevents cross-over to the intervention arm in young patients who fail to achieve return of spontaneous circulation, thereby improving the study’s quality.

To train the HEMS personnel, a mobile high-fidelity ECMO training simulation centre that offers team-based training in ECPR cannulation and management will be used. This training program is used for years to train thoracic intensivist for achieving a 24/7 in-hospital ECPR service.

Each HEMS crew member will undergo a comprehensive training program led by a minimum of three trainers for every six members, consisting of theoretical and practical elements. The training will include a-4 h E-learning sessions followed by a 6-h plenary sessions. The practical component of the training will include a 2 day training period involving hands-on experience, with each crew member performing at least 10 cannulations on a specially designed mannequin. These cannulations will be executed in high-fidelity simulations, gradually increasing in complexity and incorporating challenging scenarios that simulate uncomfortable positions and environments mirroring real-life situations. The initial training is signed off by a mannequin cannulation in a challenging condition, without errors and in a timely manner. After completion, HEMS stations will be equipped with ECPR facilities. Continuous training will follow for 6 months on a weekly basis, then ongoing sessions every 3 months. Beyond cannulation, training will encompass ECMO management and troubleshooting, facilitated by experienced perfusionists and ECMO intensivists, using real in-hospital patient to enhance skills and maintain proficiency.

To provide ongoing support to HEMS crew during and after cannulation, a 24-h telemedicine system is established. Immediately after cannulation and before transport, a mandatory live videocall is made with ECMO physicians and perfusionists.

### Treatment in the intervention group, prehospital ECPR

In the intervention group, HEMS personnel will initiate ECMO cannulation after 20 min of refractory cardiac arrest. The decision to proceed with the cannulation is made solely by the HEMS physician on the basis of the available information regarding the inclusion and exclusion criteria. Since the time it takes for ECMO initiation significantly impacts outcomes, HEMS will collect both the arrival time at the patient location and the time of ECMO flow.

Vascular access will be ascertained through an ultrasound guided puncture of the femoral artery and vein. Insertions of an 25 French venous cannula and a 17 French arterial cannula is performed followed through a Seldinger procedure using an Amplatz Super Stiff™ (with J-tip) guidewire. If they estimated weight is below 50 kg, an 21 French venous and 15 French arterial cannula is inserted(Getinge, Germany). The ECMO machine will then be connected to the cannulas to restore blood flow mechanically, after which chest compressions can be stopped. Target ECMO flow will be between 3 and 4 L per minute and a mean arterial pressure (MAP) of at least 75 mmHg measured with an invasive femoral arterial line placed in the other groin. Arterial blood pressure will be measured using a disposable Compass pressure device (Centurion Medical Products, USA). The ECMO oxygen fraction will initially be set at 0.6 with a standard sweepflow of 2L/min. Ventilation will be maintained at a tidal volume of 4 ml /kg of ideal bodyweight and a respiratory rate of 6 per minute to prevent a rapid decrease in PaCO2. Saturation levels will be measured on the right hand to detect a possible harlequin syndrome. The cannulas will be fixated, and the patient will be transported by ambulance to the nearest hospital providing ECMO care. Standard post-resuscitation care will be provided in the hospital.

### Treatment in control group, conventional CPR

The control group will receive standard advanced life support. In contrast to the current situation, the HEMS team will also be dispatched in addition to the standard dispatch of two ambulance crews. If possible, eligible patients in the control group will still be transported to a hospital with ECPR capabilities.

### Post resuscitation care

Upon admission, all patients will be transferred to the hospital’s ICU department and treated per accepted guidelines. During the first 24 h, the targeted temperature range will be maintained between 33 and 36 degrees Celsius. In addition, patients will undergo coronary angiography as soon as possible according to national guidelines if indicated.

The nationwide approach will ensure uniformity in care cessation protocols across all participating hospitals. Prognostic evaluation of post-anoxic coma and termination of care will be performed according to the national guideline, which are based on the European Resuscitation Council (ERC) and European Society of Intensive Care Medicine Guidelines [13, 14]. After 24 h, comatose patients without significant sedation can be withdrawn from life sustaining therapy if one of the criteria as described in Table 2 is met. Both the ECPR group and the control group will be evaluated on identical criteria.

**Table 2 Tab2:** Criteria to withdraw from life sustaining therapy after 24 h in comatose patients

Dilated, non-reactive pupils after 24 h *OR*
Bilateral absent N20 response on the somato-sensory evoked potentials* OR*
EEG showing highly malignant patterns after 24 h (low voltage (< 20uV)* OR*
Identical bursts suppression pattern* OR*
Generalized periodic discharges on an iso-electric ground pattern* OR*

### Devices used

At each HEMS station, a helicopter and ground vehicle are both equipped with a CardioHelp device (Getinge, Germany) for ECPR. If the weather conditions do not permit flying or the incident is close to the HEMS station, dispatch is performed by car. The same device will be used in post-resuscitation care.

### Outcome

#### Primary outcome measure

The primary outcome measure is survival at hospital discharge.

#### Secondary outcome measure

Secondary outcome measures are good favourable neurological outcome, quality-adjusted life years and health care costs.

Good neurological outcome is defined as a CPC (Cerebral Performance Categories Scale) score of 1 or 2 at 6 and 12 months. Quality-adjusted life year (QALY) is calculated at 6 and 12 months after discharge using the EQ-5D-5L tool [15]. Costs are calculated based on the use of disposables, depreciation of the ECMO machines, flight time of the helicopter and costs of institutionalisation. Healthcare costs will be calculated using the iMTA Medical Consumption Questionnaire (iMCQ) [16] and the iMTA Productivity Cost Questionnaire (iPCQ) [17]. Costs are calculated in the first 6 and 12 months after cardiac arrest.

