**Fig. 1 Fig1:**
[figure not shown]
The 10 ECPR centres with their 30 min radius

Initiating ECPR at the cardiac arrest scene could potentially overcome both problems by reducing the duration of the low-flow state and limiting thoracic compression during transport. Performing ECPR at the scene will enlarge the potential patient pool to include individuals who might not meet the criteria for in-hospital rescue therapy due to the prolonged period of low flow caused by transportation delay. With the use of the Helicopter Emergency Medical Services (HEMS), the geographic range can be extended while maintaining a short low-flow time. This perspective is the cornerstone of the ON-SCENE study.

In the Netherlands, HEMS teams consist of an anaesthesiologist or trauma surgeon, an emergency or ambulance registered nurse, and a pilot. Their primary goal is to provide specialized medical care to trauma and non-trauma patients throughout the country with an arrival at scene after approximately 11 min. Dispatching the HEMS simultaneously with the first responders after OHCA, could potentially shorten time between collaps and initiation of ECMO bloodflow which in turn could significantly improve the chance of survival compared to either conventional resuscitation without ECPR and ECPR initiated in-hospital [10].

We therefore designed and set up the ON-SCENE study to investigate the effect of equipping the HEMS with prehospital ECPR facility on hospital survival. In this HEMS setting, a nationwide coverage for prehospital ECPR in a timely manner would be achieved. The hypothesis of this study is that implementing nationwide on scene ECPR in patients with OHCA results in shorter low-flow time in comparison to regular care, which leads to improved survival rates and less neurological impairment. Despite the increased costs for delivering ECPR on scene, it is likely to be cost-effective.

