### Statistical consideration

#### Sample size

In the intervention group, the assumption is that ECPR, being initiated within 35 min after onset of cardiac arrest, thereby would result in a hospital survival of 35%. Due to an anticipated learning curve for the HEMS crews, a longer time to cannulation can be expected. The estimation is that this will cause a decrease of survival to 30% in the first 3 months.

In the control group, we assume that 30% of the patients with refractory arrest are transported to the hospital to receive ECPR and that 70% is not transported to an ECPR facility during cardiac arrest. Assumed hospital survival with ECPR in the hospital is 26% (data from Erasmus MC, Rotterdam the Netherlands) and 16% if the patient is not transported to an ECPR facility.

With the different scenarios described above, sample size was calculated using a simulation approach (R package contrast). Anticipating a possible loss of power caused by the stepped wedge design, 175 patients will be included in each study arm to detect the survival difference in mentioned above with 90% power and alpha 0.05. In total 390 patients will be included.

By extrapolating from the Amsterdam ‘ARREST’ database, we estimate that 450 patients in a year of below 50 years will have a witnessed OHCA. Assuming that 25% will fulfil the inclusion criteria, we expect that a maximum of 100 patients a year are eligible for the study. Therefore we assume that a period of 3.5 years should be sufficient to reach the needed number of patients for our study.

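### QALYs are timed from hospital discharge and costs from the cardiac arrest, so the two secondary outcomes cover different windows

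*Protocol article*

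**What the plan says.** The Secondary outcome measure section names both quantities as outcomes: "Secondary outcome measures are good favourable neurological outcome, quality-adjusted life years and health care costs". It then gives each its own time origin within one paragraph. For QALYs: "Quality-adjusted life year (QALY) is calculated at 6 and 12 months after discharge using the EQ-5D-5L tool". For costs: "Costs are calculated in the first 6 and 12 months after cardiac arrest". No other section of the article brings the two origins together.

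The Background gives the reason for collecting both: "Despite the increased costs for delivering ECPR on scene, it is likely to be cost-effective". The Statistical analysis section defines no cost-effectiveness ratio.

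The same paragraph says of neurological outcome: "Good neurological outcome is defined as a CPC (Cerebral Performance Categories Scale) score of 1 or 2 at 6 and 12 months". It gives no origin for those months.

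The Sample size section supplies the survival assumptions used below. Hospital survival is put at 35% with prehospital ECPR, with a lower value of 30% in the first 3 months. For controls, "we assume that 30% of the patients with refractory arrest are transported to the hospital to receive ECPR and that 70% is not transported". Survival is 26% with in-hospital ECPR "and 16% if the patient is not transported to an ECPR facility".

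**The concern.** Costs and QALYs are useful together only if they describe the same patients over the same period. Here the cost clock starts at the arrest, which every patient has. The QALY clock, read literally, starts at discharge, which only survivors reach and which comes later by each survivor's length of stay.

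Two things follow. First, survivors are credited with quality-adjusted time that lies after the cost window has closed. Second, the QALY origin has no date for patients who die in hospital, and survival to discharge is the outcome that the intervention is meant to change. What happens to those patients in the calculation decides both the direction and the size of any error. That choice is better fixed before outcomes are known, above all in a non-randomised study. At stake is whether the data can properly address the Background's expectation that on-scene ECPR is cost-effective.

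**Working it through.** The article states no QALY, cost or ratio figure, so there is nothing to reproduce. The check sets the two origins against each other and sizes the gap.

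**Inputs from the Sample size section**
- Intervention survival: 0.35. The lower first-3-month value is left out for simplicity.
- Control survival: 0.30 × 0.26 + 0.70 × 0.16 = 0.078 + 0.112 = 0.19.
- Difference: 0.35 − 0.19 = 0.16.

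**Assumptions not in the article**
- Utility u = 0.8 after discharge, and 0 in hospital and after death.
- Discharged patients stay alive throughout the window.
- Hospital stay L is 14, 30 or 60 days, the same in both arms.

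**Step 1: patients who never reach the QALY origin.** Intervention: 1 − 0.35 = 65%. Control: 1 − 0.19 = 81%. At 175 per arm that is 113.75 + 141.75 = 255.5, or about 256 of 350 (73%).

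**Step 2: in-hospital deaths score zero.** For a window of T years, the gain per patient is:
- discharge origin: 0.16 × u × T
- arrest origin: 0.16 × u × (T − L)

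With u = 0.8, 0.16 × 0.8 = 0.128. L is converted to years by dividing by 365.25.

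| Window | Stay | Discharge origin | Arrest origin | Excess | Ratio |
|---|---|---|---|---|---|
| 12 months | 14 days | 0.128 | 0.1231 | 0.0049 | 1.040 |
| 12 months | 30 days | 0.128 | 0.1175 | 0.0105 | 1.089 |
| 12 months | 60 days | 0.128 | 0.1070 | 0.0210 | 1.197 |
| 6 months | 14 days | 0.064 | 0.0591 | 0.0049 | 1.083 |
| 6 months | 30 days | 0.064 | 0.0535 | 0.0105 | 1.197 |
| 6 months | 60 days | 0.064 | 0.0430 | 0.0210 | 1.489 |

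The ratio is T / (T − L). The survival difference and u cancel, so under these assumptions the percentage excess depends only on the length of stay. The absolute excess scales with both.

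**Step 3: in-hospital deaths dropped.** Each arm then averages u × T over survivors only. With equal utility the 12-month difference is 0.8 − 0.8 = 0, against 0.128 per patient when everyone is counted.

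**The case against.** Several points on the other side are fair.

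- **The QALY sentence may describe only when the questionnaire is given.** It can be read that way, although the text does not say so. Even then, survivors would be assessed later than the cost cut-offs by their own length of stay, so the timing still needs aligning.
- **In-hospital deaths may well score zero.** A reader might infer that QALYs will compare survivors with survivors and lose the survival gain. The article does not support that. It nowhere restricts QALYs to survivors, scoring these deaths as zero fits its wording, and a condensed article commonly leaves such a rule to the full protocol or SAP. The error in step 3 is therefore conditional. Under zero scoring the error runs the other way and favours the intervention.
- **No cost-effectiveness ratio is defined.** This stands. The cost-effectiveness sentence is also a Background expectation that follows the stated hypothesis and is not part of it. The mismatch affects any cost-per-QALY comparison made from the two outcomes, but it does not invalidate a specified analysis.
- **The cost side should not be overstated.** A reader might infer that ECMO and intensive care are charged for every patient. The listed cost items do not name intensive care, and 70% of controls are assumed not to be taken to an ECPR facility. Only the starting point of the cost window matters here.
- **The window shift looks large if quoted per survivor.** At 30 to 60 days it is 0.8 × 30/365 = 0.066 to 0.8 × 60/365 = 0.132 QALY per survivor. Per patient, the effect on the difference between arms is 0.16 times that, or 0.011 to 0.021.

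None of this removes the conflict between the two stated origins.

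**Conclusion.** Wrong as written, and minor. The article fixes two different origins in one paragraph, and nothing elsewhere reconciles them.

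If in-hospital deaths score zero, the discharge origin overstates the QALY gain by about 0.005 to 0.021 per patient. The 12-month gain becomes 0.128 instead of 0.123 to 0.107, an excess of 4% to 20%, and the 6-month excess is 8% to 49%. These figures rest on the assumed utility and stay. A positive in-hospital utility would shrink them.

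A gain of zero would arise only if in-hospital deaths were left out of the QALY comparison, and the article does not say that they are.

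Only secondary outcomes are affected. The survival comparison and the sample size do not depend on this point.

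**What to change.** State one origin, the cardiac arrest, for both QALYs and costs. Count both over the first 6 and 12 months for all patients in each arm, with utility 0 from death. Time the remaining EQ-5D-5L and cost questionnaires from the arrest. Where an EQ-5D-5L assessment has already been timed from discharge, use its actual date in an area-under-the-curve calculation cut off at 6 and 12 months after the arrest.

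Stating the same origin for the 6- and 12-month CPC would be a useful clarification. It corrects no contradiction, because the article gives CPC no origin at all.

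The cost is a change of wording and minor re-timing of questionnaires still to be sent. No extra assessments are needed.

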#### Other data collected

In addition to the outcome measures, the following data will be collected:Baseline variables like gender, age, comorbidity.ALS-related variables: first observed rhythm, end-tidal CO_2_ before cannulation, motor score before cannulation, signs of life, total mg of adrenaline use, use of mechanical CPR.ECPR-related variables: duration of low-flow state, MAP before transport to hospital, ECMO blood flow before transport to hospital, any complication due to ECPR.In hospital-related variables: Systolic and diastolic blood pressure at and after 12 h arrival of emergency department, lactate at and after 12 h arrival of ED, use and type of unloading device, number of days at ECMO and ventilator.

### Statistical consideration

#### Sample size

In the intervention group, the assumption is that ECPR, being initiated within 35 min after onset of cardiac arrest, thereby would result in a hospital survival of 35%. Due to an anticipated learning curve for the HEMS crews, a longer time to cannulation can be expected. The estimation is that this will cause a decrease of survival to 30% in the first 3 months.

In the control group, we assume that 30% of the patients with refractory arrest are transported to the hospital to receive ECPR and that 70% is not transported to an ECPR facility during cardiac arrest. Assumed hospital survival with ECPR in the hospital is 26% (data from Erasmus MC, Rotterdam the Netherlands) and 16% if the patient is not transported to an ECPR facility.

With the different scenarios described above, sample size was calculated using a simulation approach (R package contrast). Anticipating a possible loss of power caused by the stepped wedge design, 175 patients will be included in each study arm to detect the survival difference in mentioned above with 90% power and alpha 0.05. In total 390 patients will be included.

By extrapolating from the Amsterdam ‘ARREST’ database, we estimate that 450 patients in a year of below 50 years will have a witnessed OHCA. Assuming that 25% will fulfil the inclusion criteria, we expect that a maximum of 100 patients a year are eligible for the study. Therefore we assume that a period of 3.5 years should be sufficient to reach the needed number of patients for our study.

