## Methods

### Trial design

This is a nationwide multicentre, prospective, interventional, non-randomised stepped wedge study that evaluates the effect of prehospital ECPR in patients with witnessed OHCA between the age of 18 and 50 years old versus conventional HEMS care without ECPR. The study started end of 2021 and is scheduled to finish by the end of 2025.

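### The sample size section gives two enrolment targets, 350 (175 per arm) and 390, with nothing to link them, and the stated accrual period fits only 350

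*Protocol article*

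**What the plan says.** All the enrolment figures stand in the Sample size section of the protocol article. For the stated survival assumptions, "175 patients will be included in each study arm to detect the survival difference in mentioned above with 90% power and alpha 0.05". The clause just before this mentions a possible loss of power from the stepped-wedge design, without a figure, as part of the reasoning for the 175. The next sentence reads: "In total 390 patients will be included".

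On accrual, the section starts from 450 witnessed arrests a year in the age group, takes 25% as eligible, and concludes that "we expect that a maximum of 100 patients a year are eligible for the study". It then says that "we assume that a period of 3.5 years should be sufficient to reach the needed number of patients for our study". The needed number is not repeated there, so the reader cannot tell whether 350 or 390 is meant.

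The calendar is in Trial design: "The study started end of 2021 and is scheduled to finish by the end of 2025". The Secondary outcome measure section sets CPC at 6 and 12 months, QALYs at 6 and 12 months counted from discharge, and costs over the first 6 and 12 months after the arrest. Allocation of patient adds that dispatch centres not ready at the start were kept out until they were, and that an amendment to lengthen the study period was filed. The length of that extension is not given.

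**The concern.** A trial has one enrolment target, and it settles when recruitment ends. Here two targets 40 patients apart stand in consecutive sentences, and the accrual sentence that follows agrees with only one of them.

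The stake is the stopping point rather than power. Crews know which treatment is in use, and the primary test is an unadjusted chi-square on survival at discharge, an outcome known soon after each inclusion. With both figures published, recruitment could end at 350 or at 390 and either could be called the plan. The document should not leave that choice open to a time when survival by group may be known. A mismatched duration also leaves the end date, and with it the completeness of the 12-month outcomes, without a firm basis.

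**Working it through.** **Inputs** (protocol article, Sample size, unless noted)
- Intervention survival 35%, with this qualification for the learning period: "The estimation is that this will cause a decrease of survival to 30% in the first 3 months".
- Control group: "30% of the patients with refractory arrest are transported to the hospital to receive ECPR and that 70% is not transported". Survival is 26% with in-hospital ECPR and 16% without transport.
- Power 90%, alpha 0.05. Sidedness is not stated; two-sided is assumed because the primary test is a chi-square.
- 450 arrests a year, 25% eligible, at most 100 a year, 3.5 years.
- Window from end of 2021 to end of 2025, about 4 years (Trial design).
- Longest follow-up 12 months (Secondary outcome measure).

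**1. Does 175 per arm reproduce?**
- Control survival = 0.30 × 26% + 0.70 × 16% = 7.8% + 11.2% = 19.0%.
- n per arm = [1.960 × √(2 × 0.27 × 0.73) + 1.282 × √(0.35 × 0.65 + 0.19 × 0.81)]² / 0.16² = 160. With continuity correction it is 172.
- If 10% of intervention patients have 30% survival, the intervention average is 34.5% and n = 170. If 20% do, it is 34.0% and n = 180.

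So 175 is consistent with the stated rates. The cluster and period settings of the simulation are not in the article, so the stepped-wedge allowance itself cannot be checked.

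**2. Does 390 follow?**
- 2 × 175 = 350, and 390 − 350 = 40, which is 40/350 = 11%.
- 175/(1 − 0.10) = 194.4, rounded up to 195; 2 × 195 = 390.

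The total therefore appears if a 10% loss is assumed. No such loss is stated.

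**3. Which target does the accrual statement fit?**

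| Rate per year | Inclusions in 3.5 years | Years for 350 | Years for 390 |
|---|---|---|---|
| 100 (stated maximum) | 350 | 3.50 | 3.90 |
| 112.5 (450 × 0.25) | 394 | 3.11 | 3.47 |

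At the stated maximum, 3.5 years gives exactly 350. It gives 390 only at the unrounded rate, which exceeds the stated maximum.

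**4. Does the calendar hold?**
- Inclusions only: 4 years × 100 = 400. This covers 390 with about 0.1 year to spare, if every month recruits at the ceiling.
- Inclusions plus 12 months at 100 a year: 3.5 + 1 = 4.5 years for 350; 3.9 + 1 = 4.9 years for 390.
- The same at 112.5 a year: 3.11 + 1 = 4.11 years; 3.47 + 1 = 4.47 years.

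All four exceed 4 years. With the last 12 months kept for follow-up, the window holds 3 × 100 = 300 inclusions, so 50 patients (target 350) or 90 (target 390) would be included too late for a 12-month visit. Only survivors need that visit. At the average assumed survival of (35% + 19%)/2 = 27%, this is about 14 or 24 people.

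**5. Does the choice of target change power?** Plain two-proportion test, two-sided:

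| Intervention survival (control 19%) | 175 per arm | 195 per arm |
|---|---|---|
| 35% | 92.4% | 94.8% |
| 34.5% | 90.9% | 93.6% |
| 34% | 89.2% | 92.2% |

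The plan's figure of 90% corresponds to 350. A total of 390 adds 2 to 3 points.

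**The case against.** The best defence is that 390 is 350 with an ordinary 10% allowance. Table 1 removes some patients after inclusion (active malignancy, recent cerebrovascular accident, a do-not-resuscitate order found later), and Ethical considerations relies on deferred consent for use of data, so a loss is foreseeable. That is plausible, but it is an inference: the article names no loss. The stepped-wedge allowance cannot fill the gap because it is already part of the 175.

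A second defence is that the sponsor saw the recruitment problem and filed an extension. This stands, and it counts against reading the end date as an oversight. The article does not say how long the extension is or whether end of 2025 already includes it, so the two durations remain unreconciled.

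Several stronger readings are tempting, and the documents do not support them:
- **That 390 cannot be reached.** Four years at 100 a year gives 400, and 3.5 years at 112.5 gives 394. It is reachable, but without margin.
- **That 12-month outcomes will certainly be cut off.** This holds only if the finish means last follow-up. If it means last inclusion, there is no conflict. The primary outcome, survival at discharge, is hardly touched in either case.
- **That the extra 40 patients would all be intervention patients.** Late patients in a stepped wedge tend to be, but the timetable figure is not shown and the text gives no switch dates.
- **That the trial is underpowered at 350.** Step 5 shows otherwise.
- **That rounding 112.5 down to 100 is a design error.** It is a cautious rounding of a rough extrapolation. It matters only because the two rates point to different targets.

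**Conclusion.** The contradiction stands. The Sample size section states 350 and 390 as targets, a gap of 40 patients or 11%, with no stated step from one to the other. The stated duration at the stated maximum rate fits 350; 390 needs 3.9 years, which fits the roughly 4-year window only if recruitment runs at the ceiling throughout, despite the late dispatch centres.

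The follow-up point is conditional. If the end-2025 finish is the last follow-up visit, 12-month CPC, QALYs and costs cannot be complete for 350 (about 4.5 years needed) or for 390 (about 4.9), at 100 a year. The text leaves this open.

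The 175 per arm and its 90% power are not in dispute; they reproduce approximately under a two-sided test without clustering. The defect is a contradictory target and a mismatched duration, and its consequence is an undefined stopping point.

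**What to change.** In the Sample size section:
1. State one total and derive it: either 350 as 2 × 175, or 390 as 2 × 195 with the 10% loss named and its source given (removal after inclusion, consent not obtained, or other).
2. Use one annual rate and give the accrual period that follows from it, for example 350/100 = 3.5 years or 390/100 = 3.9 years, with any allowance for late-joining dispatch centres and for the filed extension.

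In Trial design:

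3. Replace the single finish date with two dates, last inclusion and last 12-month follow-up, and say whether they include the extension.
4. State whether recruitment ends at a fixed number or on a fixed date, and record this before any comparison of outcomes between groups.

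The cost is a few sentences. Keeping 350 requires no extra patients, and 390 is already one of the published totals. The 12-month outcomes may require a later date for the end of follow-up, depending on what the present date means.
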